3. Subgroup analyses	The percentage of women within each of the normal, overweight, and obese BMI categories will be similar with respect to being with the IOM target GWG for each category	Proportion of women in each BMI category who reach appropriate GWG according to the IOM guideline for GWGs	Regression analysis including the interaction term of BMI group X Intervention group
4. Sensitivity analyses	Combined Nutrition + Exercise Intervention leads to a greater percentage of women who achieve GWG within current recommendations when compared to standard care	Primary outcome only	***•*** Generalized estimating equations ***•*** Random-effects model

IMPORTANT REMARKS:

In all analyses, results will be expressed as difference or OR (95% CI) and associated *p* values, as appropriate

Bonferroni method will be used to adjust the overall level of significance for multiple secondary outcomes

We will examine residuals to assess model assumptions

The GEE [76] is a technique that allows to specify the correlation structure between patients within a site and this approach produces unbiased estimates under the assumption that missing observations will be missing at random. An amended approach of weighted GEE will be employed if missingness is found not to be at random [77]

*Infant growth outcomes at 6 months will be adjusted for feeding type (duration of breast feeding from birth to 6 months)

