### Statistical methods

The analysis and reporting of the results will follow the SPIRIT statement for reporting RCTs [53]. The process of patient selection and flow throughout the study will be summarized using a flow-diagram (Fig. 2).

The results of patient baseline characteristics and outcome variables (both primary and secondary) will be summarized using descriptive summary measures: expressed as mean (standard deviation) or median (range) for continuous variables and n (%) for categorical variables. All statistical tests will be performed using two-sided tests at the 0.05 level of significance. Binary outcomes will be analyzed using logistic regression and continuous outcomes will be analyzed using linear regression. All analyses will account for stratification by including study site and participants’ BMI category in the models. For all models, the results will be expressed as estimate of the difference for continuous outcomes (odds ratio [OR] or relative risk [RR] for binary outcomes), corresponding two-sided 95% confidence intervals (CI) and associated *p* values. *P* values will be reported to three decimal places with values < 0.001 reported as < 0.001. The Hosmer–Lemshow will be used to assess goodness-of-fit for logistic regression and explore the residuals to assess goodness-of-fit and model assumptions for linear regression.

An intention-to-treat principle will be adopted to analyze all outcomes. Multiple-imputation will also be used to handle missing data during data collection. Sensitivity analyses will be performed using some of the commonly used RCT patient-level methods (e.g. generalized estimating equations, the random-effect model which account for the potential correlation within sites, etc.) to assess the robustness of the results [54]. All the analyses will be done using SAS 9.2 (Cary, NC, USA) or SPSS 13 (Chicago, IL, USA). Table 2 provides a summary of the planned methods of analyses for each outcome and subgroup.

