For the timely recruitment of study participants, challenges included prolonged ethics approval processes at secondary recruitment sites, reduced recruitment at community family practices due to influx of immigrants who were non-English speaking (thus not eligible), and competition with other studies sampling pregnant women. In light of these, we have taken measures to achieve the predetermined sample size based on a power analysis for the primary outcome so that the integrity of the study is preserved and the results are able to properly test the stated hypothesis and provide the needed new knowledge. To expand recruitment at McMaster University a new local study site was set up in a nearby city, Burlington, Ontario, with the collaboration of midwifery and obstetric clinics, as well as the local hospital. This partnership is very successful thus helping to achieve the recruitment goal. To date, retention after randomization to the study visit at 36–38 week of gestation when we assessed our primary outcome is 87%. To maximize retention of participants, we implemented a number of procedures such as study visit times at the convenience of the participants, including home visits. We also offered in-person, over the phone, and email correspondence to keep participants engaged. For participants in the intervention group, providing them with the dairy products (which are an integral part of the intervention) increases the likelihood of consuming the recommended amount. For the exercise component, participants receive a free pedometer as a self-motivation tool to reach their step count goals. Lastly, for both groups, participants are compensated on three occasions with $25 gift cards that they can redeem at a local grocery store.

If effective, this RCT will generate high-quality evidence to refine the nutrition guidelines during pregnancy to improve health of women during pregnancy and their offspring in early life, including acquisition of a strong skeleton.

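### Table 2's remarks attach the wrong missing-data assumptions to the GEE sensitivity analysis: unweighted GEE is not generally unbiased under missing at random, and weighted GEE does not correct data missing not at random

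*Protocol article*

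**What the plan says.** The Statistical methods section makes logistic regression the analysis for binary outcomes ("Binary outcomes will be analyzed using logistic regression and continuous outcomes will be analyzed using linear regression") and fixes the covariates: "All analyses will account for stratification by including study site and participants’ BMI category in the models". It names imputation separately: "Multiple-imputation will also be used to handle missing data during data collection". GEE comes in only as a robustness check ("Sensitivity analyses will be performed using some of the commonly used RCT patient-level methods"), and Table 2 limits it to the primary outcome.

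The remarks under Table 2 (section Outcome measurements) describe that check. The cluster is the site: "The GEE [76] is a technique that allows to specify the correlation structure between patients within a site". They then say that "this approach produces unbiased estimates under the assumption that missing observations will be missing at random", and add: "An amended approach of weighted GEE will be employed if missingness is found not to be at random".

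On the amount of missing data, the Discussion reports that "retention after randomization to the study visit at 36–38 week of gestation when we assessed our primary outcome is 87" percent. This is an interim figure while recruitment continues, and it is not split by arm.

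**The concern.** The two sentences on GEE describe a ladder: ordinary GEE for data missing at random, weighted GEE for data that are not. On the standard definitions both steps are one rung too high. Unweighted GEE needs data missing completely at random, or missingness that depends only on covariates in the outcome model. Inverse-probability weighting is what extends GEE to missing at random. Neither reaches missingness that depends on the unobserved outcome.

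The switch between them is also unworkable as written. Missing at random and missing not at random can fit the observed data equally well, so no analysis of those data can establish the second.

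What is at stake is how the sensitivity analysis is interpreted. The trial is open-label, the outcome is weight gain, and only the intervention arm has weekly or biweekly visits, so dropout related to arm and weight gain is plausible. Followed as written, an unweighted GEE could be reported as safe under missing at random, and a weighted GEE as protection against non-random dropout, when neither claim is true.

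**Working it through.** The article gives no figure on this point to reproduce. The check is one line of theory followed by a simulation.

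**Inputs from the protocol article**
- Model covariates: arm, site, BMI category (Statistical methods).
- One binary primary outcome per woman; cluster = site (Table 2 and its remarks).
- Weight at 26–28 weeks is measured in all participants but is not in the model (Data and biosample collection).
- Retention to the 36–38 week visit: 87% so far (Discussion).

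**Theory.** Let R = 1 if the outcome y is observed, X = model covariates, L = weight gain by 26–28 weeks, μ = E(y | X).
- Unweighted: the estimating equation is centred at zero if E[R(y − μ) | X] = 0. Under missing at random this expectation equals cov(P(R=1 | X, L), y | X). It is zero if P(R=1) depends on X only, and generally not zero if it also depends on L, because L predicts y.
- Weighted by 1/π, with π = P(R=1 | X, L): if R does not depend on y given X and L, then E[(R/π)(y − μ) | X] = 0 and the bias is removed.
- If R depends on y itself, P(R=1 | X, L, y)/π still varies with y, the expectation is not zero, and weights built from observed data leave bias.

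**Simulation.** All effect sizes and mechanisms are assumptions, because the article gives none.
- n = 400,000; two arms, two sites and three BMI groups of equal size (a simplification of the four strata).
- L ~ N(0,1) − 0.6·arm.
- logit P(y=1) = −0.1 + 0.5·arm − 0.9·L + 0.1·site − 0.2·(BMI group − 1), with BMI group coded 0, 1, 2.
- Retention is logistic in the term shown, with the intercept set to give 87%.
- Outcome model: arm, site, BMI. With an independence working correlation, the GEE point estimates equal those of logistic regression.
- Weights: from arm, L, arm × L, site and BMI.

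| Missingness (term in logit of retention) | Unweighted: log OR / risk difference | Weighted: log OR / risk difference |
|---|---|---|
| None missing (truth) | 0.898 / 0.212 | – |
| Completely at random | 0.898 / 0.212 | 0.899 / 0.212 |
| Model covariates only (0.5·arm − 0.5·top BMI group) | 0.903 / 0.213 | 0.902 / 0.213 |
| At random via L, intervention arm only (−1.2·L) | 1.008 / 0.234 | 0.904 / 0.213 |
| At random via L, both arms (−1.0·L) | 0.875 / 0.202 | 0.905 / 0.213 |
| Depends on y, both arms (1.5·y) | 0.896 / 0.202 | 0.901 / 0.204 |
| Depends on y, intervention arm only (2.0·(y − 0.5)) | 1.194 / 0.270 | 1.156 / 0.263 |

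**Reading the table**
- Missing at random, unweighted: 0.234 − 0.212 = +2.2 points, or 0.202 − 0.212 = −1.0 point. Weighting brings both to within 0.1 point.
- Dependent on y in one arm: unweighted +5.8 points (0.270 − 0.212), weighted still +5.1 points (0.263 − 0.212). Weighting removes 0.7 of the 5.8 points.
- Dependent on y equally in both arms: the odds ratio is nearly preserved, but the weighted arm proportions are 0.531 and 0.735 against true values of 0.489 and 0.700.

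**The case against.** **Loose terminology.** The strongest defence is that the remarks write missing at random where they mean missing completely at random. Both sentences then become sensible: ordinary GEE under the stronger assumption, weighted GEE when dropout depends on observed data. Departure from missing completely at random can also be looked for in the data. This reading is possible, since the article defines neither term. The wording would still name the wrong assumption and need correcting. A trigger based on detection would also remain weak: if the interim rate held, about 0.13 × 242 = 31 outcomes would be missing, too few for a null finding to be reassuring.

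**Limited scope.** This stands. GEE is a sensitivity analysis of one outcome, clustered by site rather than over repeated visits. If missingness depends only on arm, site and BMI category, unweighted GEE is consistent. A reader might infer that the primary analysis or the whole missing-data strategy is invalid. The article does not support that: the primary analysis is logistic regression, and multiple imputation is planned separately and can be valid under missing at random with an adequate imputation model.

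**Omission.** A reader might also infer that the trial has no analysis for non-random missingness. That cannot be concluded: the imputation model and any tipping-point analysis are commonly left to the full protocol or SAP, which is not shown. The point here is what the remarks state, not what they leave out.

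**Size.** It is tempting to multiply 13% missing by a supposed gap between dropouts and completers and call the result this trial's bias. The article gives no such gap and no split of retention by arm. Such a figure would also measure complete-case bias in general rather than the effect of these two sentences.

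**Conclusion.** The point holds as an error in the stated properties of the sensitivity analysis. On standard definitions, unweighted GEE is not generally unbiased under missing at random, weighted GEE with weights from observed data does not correct data missing not at random, and the condition for switching cannot be established from observed data.

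No size can be given for this trial. Under the assumed mechanisms at 87% retention, the errors in the risk difference were +2.2 and −1.0 points for unweighted GEE under missing at random, and +5.1 points for weighted GEE when missingness depended on the outcome in one arm. The existence of bias follows from theory; its size and direction depend on the mechanism. The error matters in practice only if dropout depends on something outside the model, such as the 26–28 week weight or the outcome itself.

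**What to change.** In the remarks under Table 2:

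1. State that unweighted GEE and complete-case logistic regression assume missingness depends only on the model covariates (arm, site, BMI category).
2. Name the missing-at-random analysis: either weighted GEE, with weights that include arm and the 26–28 week weight, or the multiple imputation already planned. Run it regardless of any test of missingness.
3. Delete the claim that weighted GEE handles non-random missingness, together with its trigger.
4. If robustness to non-random missingness is to be claimed, replace that fallback with delta-adjusted imputation of the primary outcome, shown as a tipping-point table with the shift varied separately by arm.

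The cost is a wording change and, if step 4 is taken, one extra table. All of it uses data already collected and leaves the primary analysis unchanged.

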### Randomization: allocation and implementation

Block randomization is used with block sizes of two, four, and six selected at random, using an online Research Electronic Data Capture (REDCap) randomization service managed by an independent team in the Biostatistics Unit at St Joseph’s Healthcare in Hamilton, ON, Canada. Randomization to the two study arms occurs in a 1:1 ratio and is stratified by study site and pre-pregnancy BMI category following IOM guidelines (underweight: BMI < 18.5, normal weight: BMI 18.5–24.9, overweight: BMI 25.0–29.9, and obese: BMI ≥ 30.0 kg/m^2^). The eligibility of participants is confirmed at the first visit, when baseline data are also collected. The research assistant randomizes the participant at the second visit to the study center using an online third-party automatic randomization system. Once randomized, the research assistant consents the participant to the appropriate study arm at a time that is 14–17 weeks/6 days of gestation. Assessments, regardless of the study arm, occur at < 18 weeks of gestation, 26–28 weeks of gestation, 36–38 weeks of gestation, birth, three months postpartum, and six months postpartum. The intervention arm consists of weekly or biweekly in-person visits (based on the participant’s preferences) during pregnancy (i.e. from allocation to study group until 36–38 weeks of gestation). Baseline measures (i.e. before randomization), primary and secondary outcome measures, and other measures assessed during and after pregnancy are measured in all participants, regardless of their study group allocation.

The flow diagram (Fig. 2) will be included in future published results.

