		1. Controlled walking program with the study nutritionist a. 25 min per session, 3–4 times per week, while increasing the time by 2 min/week to a maximum of 40 min maintained until delivery [39] 2. 10,000 steps per day a. Daily step counts and any other exercise tracked using a pedometer every day and an exercise log. Also used as a motivator and self-monitoring device which will also help improve compliance [39]
Wellbeing during pregnancy	**Nested qualitative study**	
	1. Focus group and information session given by a midwife in the third trimester of pregnancy a. Discussion on topics such as pain relief options during labor and breastfeeding techniques	

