Participants randomized to the usual care group (control) receive usual prenatal care. Participants are given the most recent advice from Health Canada including Healthy Weight Gain During Pregnancy [17], the Pregnancy Weight Gain Calculator [44], and Eating Well with Canada’s Food Guide [46]. Mothers are followed by their primary care provider who also receives the same Health Canada materials. After delivery, they are followed by their healthcare practitioners. In addition, the control participants are invited to participate in a focus group and to attend an information session led by a midwife; topics discussed include pain relief options during labor and breastfeeding techniques (Table 1).

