Physical activity level is assessed through wearing a BodyMedia Sensewear Pro II armband monitor device (BodyMedia, Pittsburgh, PA, USA) in all participants for the same three days (as food monitoring above) in their work/home environment. These small devices are comfortable and easily wearable on the arm [38]. The data collected for three days at each visit (12–17, 26–28, and 36–38 weeks of gestation and six months postpartum) includes daily steps, daily energy expenditure, and minutes of activity level in Metabolic Equivalent of Task (MET; very vigorous, vigorous, moderate, sedentary). The Sensewear unit does not provide feedback to the participant.

Pregnancy and infant outcomes are obtained from participant’s medical records. Details are extracted about Cesarean section and/or vaginal delivery. For infant outcomes, data regarding gestational age, birth weight, birth length, birth head circumference, 1-min and 5-min Apgar scores, complications related to birth, and feeding practices at birth are extracted.

Infant weight and length at birth are recorded from medical charts and at three months of age as reported by the mother during the telephone interview. At the six-month visit, trained assessors measure infant weight by electronic scale (Medela BabyWeigh, McHenry, IL, USA), length using a measuring board for term infants (Pediatric Stadiometer, Ellard Instrumentation Ltd., Monroe, WA, USA), and head circumference using a constant-tension measuring tape (OHAUS, Dundas, ON, Canada), following standard operating procedures.

Infant feeding practices over the first three months are recorded by phone call and at six months in person using a standardized questionnaire administered by a trained assessor [51]. The questionnaire includes feeding history, duration and extent of breastfeeding, introduction of solid foods, and use of vitamins and supplements.

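### Six-month infant growth outcomes are to be adjusted for breastfeeding duration, which arises after randomisation and which allocation can affect, so the stated analysis does not target the total effect of assignment

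*Protocol article*

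**What the plan says.** The protocol article, in the remarks below Table 2 (Outcome measurements), fixes the covariate: "Infant growth outcomes at 6 months will be adjusted for feeding type (duration of breast feeding from birth to 6 months". It states no model without feeding alongside this one, and it does not call the adjusted model exploratory, supportive or a mediation analysis. The sensitivity analyses in Table 2 are confined to the primary outcome.

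On timing, the section on randomization says: "The research assistant randomizes the participant at the second visit to the study center using an online third-party automatic randomization system". That visit falls at 14 weeks to 17 weeks and 6 days of gestation. The section on data and biosample collection says: "Infant feeding practices over the first three months are recorded by phone call and at six months in person".

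On what each arm is offered, the Interventions section says of usual care that "the control participants are invited to participate in a focus group and to attend an information session led by a midwife", and that "topics discussed include pain relief options during labor and breastfeeding techniques". The wellbeing row of Table 1 lists "Focus group and information session given by a midwife in the third trimester of pregnancy" under a nested qualitative study. No such session is described for the intervention arm.

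On the analysis principle, Statistical methods says: "An intention-to-treat principle will be adopted to analyze all outcomes". The only covariates it names for all models are study site and BMI category.

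**The concern.** A covariate fixed before randomisation can be added to the model without changing what the arm coefficient means in a linear model. A variable that arises afterwards, and that allocation may move, is different. Conditioning on it does two things:

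- It subtracts any part of the treatment effect that operates through the variable.
- It makes the arms non-comparable on unmeasured causes of both the variable and the outcome. Randomisation had balanced those causes.

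Breastfeeding duration fits this description. It accrues only after birth, and a session that touches on it is described for one arm only. It plausibly shares causes with infant growth, such as maternal education, maternal health or infant vigour; these examples are not from the protocol.

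At stake is the reading of the trial's six-month infant weight z-score and fat mass results. Offspring obesity is part of the stated rationale, and the only analysis described for these outcomes would not answer what assignment to the programme does to them.

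**Working it through.** **No figure to reproduce.** The point concerns a model choice, and the protocol gives no arm difference in feeding, no effect of feeding on growth and no SD. The size is therefore illustrated over a range of assumed values.

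**Model.** Let A be arm (1 = intervention), M breastfeeding duration in SD units, Y the infant outcome, and U an unmeasured cause of both. There is no direct effect of A on Y.

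- M = −gA + uU + error, with variance of M within arm equal to 1
- Y = bM + cU + error, with error SD 1

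**Formulas.**

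- Total effect of assignment, estimated by the model without feeding: −gb
- Within-arm slope of Y on M: b + cu
- Breastfeeding-adjusted arm coefficient: −gb + g(b + cu) = gcu
- Deviation of the adjusted estimate from the total effect: gcu − (−gb) = g(b + cu)

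**Assumed range.** g = 0, 0.2, 0.4; b = 0 or −0.2; (u, c) = (0, 0), (0.4, 0.4) or (0.4, −0.4), so cu = 0 or ±0.16.

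| Setting | Total effect | Adjusted estimate | Deviation |
|---|---|---|---|
| g = 0, any b, u, c | 0 | 0 | 0 |
| b = −0.2, no U, g = 0.2 / 0.4 | 0.04 / 0.08 | 0 / 0 | −0.04 / −0.08 |
| b = 0, cu = ±0.16, g = 0.2 / 0.4 | 0 / 0 | ±0.03 / ±0.06 | ±0.03 / ±0.06 |
| b = −0.2, cu = +0.16, g = 0.2 / 0.4 | 0.04 / 0.08 | 0.03 / 0.06 | −0.01 / −0.02 |
| b = −0.2, cu = −0.16, g = 0.2 / 0.4 | 0.04 / 0.08 | −0.03 / −0.06 | −0.07 / −0.14 |

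The largest entry is 0.4 × (−0.2 − 0.16) = −0.144. A simulation with 2,000,000 records per setting agreed with the formulas to within about 0.003. In it the model without feeding recovered the total effect in every setting.

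**Units.** These are multiples of the outcome's error SD. In the worst case the within-arm variance of Y is 1 + 0.04 + 0.16 + 2(−0.2)(−0.4)(0.4) = 1.264, so its SD is 1.12. The deviation is then 0.144/1.12 = 0.13 of the full within-arm SD.

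**Scale against the trial.** Power calculation gives 240 participants in total for the infant bone outcome, with a 15% attrition allowance but no effect size. At two-sided 0.05 and 80% power, the detectable difference is (1.960 + 0.842) × √(4/N). This is 0.36 SD at N = 240 and 0.39 SD at N = 240 × 0.85 = 204. The worst assumed case is about a third of that, and most cases are far smaller.

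**False-positive rate.** With 206 infants, no true effect, b = 0, u = c = 0.4 and 4,000 replicates, the adjusted model rejected in 4.8%, 4.9% and 6.9% of trials at g = 0, 0.2 and 0.4. The model without feeding stayed between 4.7% and 4.9%. The simulation standard error is √(0.05 × 0.95/4000), about 0.3 percentage points. Only the rise at g = 0.4 is clear.

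**Limit.** The arithmetic is for a linear model. Table 2 marks infant body fat mass as binary. The argument is the same there, but the size would be on the log-odds scale.

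**The case against.** The best defence is that the trial asks about programming in utero, so the investigators may want the prenatal effect separated from postnatal feeding. The midwife session belongs to a nested qualitative study, and an unadjusted contrast would carry any effect of that add-on. This is a legitimate question, but it concerns a direct effect. Answering it requires no unmeasured confounding between feeding and growth, which the protocol does not state. It supports keeping the adjusted model, though not as the only stated one.

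Several stronger readings are tempting, and the document does not support them:

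- A reader might infer that the adjustment contradicts the intention-to-treat statement. It does not do so literally. Intention to treat fixes who is analysed and in which arm, and naming site and BMI category does not exclude other covariates. What changes is the quantity estimated.
- A reader might infer that bias is established. It depends on the arms differing in breastfeeding duration, and the document gives no evidence that they will. Controls are only invited to the session, breastfeeding is one topic, and uptake is not given. The intervention counselling is described in terms of energy, protein and dairy, not breastfeeding.
- A reader might extend the point to infant bone. The remark says growth outcomes and does not clearly reach bone mineral content.
- A reader might take this for a central claim of the trial. The stated objectives are gestational weight gain and bone status. The Abstract lists infant weight z-scores and fat mass as secondary, whereas the Outcome measurements list puts infant body fat among other outcomes.

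A fuller analysis plan may add a model without feeding. The remark as published is nevertheless unqualified.

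**Conclusion.** The point holds in a limited and conditional form. The protocol fixes a post-randomisation covariate for six-month infant growth outcomes and itself describes a route by which allocation could change it. If breastfeeding duration differs by arm, the stated analysis does not estimate the total effect of assignment and can be biased by shared causes of feeding and growth. If it does not differ, the adjusted estimate is unbiased.

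The timing of the covariate and the control-only invitation rest on the text. The size, 0 to about 0.14 SD, rests entirely on assumed values: arm differences in feeding up to 0.4 SD, a feeding effect of 0 or −0.2, and a shared cause with loadings of 0.4. Within that range the distortion is small to moderate for a lower-tier outcome. Gestational weight gain is unaffected.

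**What to change.** Reword the remark under Table 2 so that:

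1. The main analysis of six-month infant weight z-score and fat mass contains arm, site and maternal BMI category. Infant sex and age at measurement may be added for precision. Age at measurement is not strictly a pre-randomisation variable, so its inclusion rests on the judgement that arm does not plausibly affect it.
2. The breastfeeding-adjusted model is kept and labelled as a supportive or mediation analysis, with its assumption of no unmeasured confounding between feeding and growth stated.
3. Breastfeeding duration is reported by arm, so that readers can see whether the two models could diverge.

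The remark should also say whether it is meant to apply to infant bone outcomes.

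The cost is a few lines of text. The feeding data are already collected by phone and at the six-month visit. The one downside is a possible small loss of precision if feeding explains some of the outcome variance.
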